## Abstract

**Background:**

The National Institutes of Health estimates the prevalence of insomnia in menopausal women at 40–50%. Some studies have shown that acupuncture might be effective in treating primary insomnia and insomnia related to depression and stroke. Although there are some programs supporting insomnia during the menopausal transition, there are few randomized controlled trials (RCT) to provide evidence regarding their effectiveness. We design a RCT of suitable sample size to verify the effectiveness of acupuncture in patients with insomnia during the menopausal transition and to form an optimized acupuncture treatment protocol.

**Method/Design:**

In this randomized, single-site, single-blind, placebo-controlled trial, 84 eligible patients will be recruited and randomly assigned to either the acupuncture group (*n* = 42) or the sham control group (*n* = 42) in a 1:1 ratio. Participants will receive a total of 18 treatment sessions for eight consecutive weeks. Treatments will be given three times per week in the first four weeks, twice a week for the next two weeks, and finally once weekly for the final two weeks. Treatment will utilize eight main acupoints (GV20, GV24, GV29, RN6, RN4, SP6, HT7, EX-HN22) and extra two acupoints based on syndrome differentiation. The primary outcome will be assessed using the Pittsburgh Sleep Quality Index (PSQI). The secondary outcomes will be measured by sleep parameters recorded in the Actigraphy (SE, TST, SA), Insomnia Severity Index (ISI), Self-Rating Anxiety Scale (SAS), Self-Rating Depression Scale (SDS), and Menopause Quality of Life (Men-QOL). The primary outcomes will be assessed at baseline, week 4, week 8, and the first and third month after the end of treatment.

**Discussion:**

If the results confirm that acupuncture is effective and safe for the treatment on insomnia in menopausal women, this positive outcome could provide evidence for clinical application.

**Trial registration:**

Chinese Clinical Trial Registry, ChiCTR1800018645. Registered on 10 January 2018.

## Background

The menopausal transition (MT) is often accompanied by a myriad of symptoms, the most common being insomnia [1–3]. Insomnia is characterized by having difficulty falling asleep, frequent nocturnal waking with difficulty falling back asleep [4], and unexplained pain. A study conducted by the National Institutes of Health estimates the prevalence of insomnia in menopausal women at 40–50% [5–8]. Women who experience poor sleep quality during the MT are more likely to have critical problems [9] such as depression, anxiety, memory and cognitive deprivation, cardiovascular disease, and reduced quality of life [3, 4]. Still, there are few effective therapies available for treating sleep problems during the MT. Yoga, therapeutic massage, and exercise may be helpful for sleep disorders, but they have not yet been proven as an effective independent treatment [10]. Hormone therapy (HT) is currently the most effective treatment but is also associated with a number of risks [11, 12]. HT can reduce hot flashes at night; some studies have reported that it can reduce sleep disorders [13]. However, increasing numbers of women are refusing HT due to the risks (myocardial infarction, stroke, venous thromboembolism, and breast cancer) outlined by trials published in the Women’s Health Initiative [14]. Moreover, these trails reported that HT has a weaker effect on insomnia than previously thought [15] .

Acupuncture, an important part of traditional Chinese medicine (TCM), has been used for thousands of years in China to treat various diseases including sleep disorders [5]. Many studies have confirmed the efficacy of acupuncture for primary insomnia and related depressive disorders [16–18]. Based on results of the efficacy of acupuncture for depression-related insomnia [19] and insomnia following stroke [20], we believe that acupuncture might be an effective treatment for insomnia during the MT. However, effects of acupuncture on sleep disorders remain uncertain because of flawed research methodology, such as improper sample size, treatment times, and follow-up problems [21].

The main objective of this study is to determine whether acupuncture is effective as compared to a sham acupuncture control on insomnia in menopausal women. The findings of this trial will provide useful information in forming an optimal acupuncture treatment protocol.

## Methods/Design

### Hypotheses

Acupuncture treatment helps menopausal transition insomnia patients improve their sleep quality and other related symptoms.

### Objectives

To compare the differences in improvement of insomnia, assessed by the Pittsburgh Sleep Quality Index (PSQI) and Insomnia Severity Index (ISI), between the intervention group and control group.To compare the differences in improvement of mood, measured by the Self-Rating Anxiety Scale (SAS) and Self-Rating Depression Scale (SDS), between the intervention group and control group.To compare the differences in improvement of Menopause Quality of Life (MenQOL), between the intervention group and control group.

### Design

This is a single-site, single-blind, randomized, placebo-controlled clinical trial that will be carried out in the Shanghai Municipal Hospital of Traditional Chinese Medicine. Eligible patients will be randomly divided into the acupuncture group and the sham acupuncture group in a 1:1 allocation ratio. All participants will sign the informed consent before proceeding with the trial. The flow chart of the study process is as follows in Fig. 1. Timing of treatment assessments and data collection are as follows in Table 1.

**Fig. 1 Fig1:**
[figure not shown]
Flowchart of the trial

**Table 1 Tab1:** Timing of treatment assessments and data collection

	Study period					
	Enrolment	Baseline	Treatment phase		Follow-up phase	
Timepoint^a^	–1 week	0 weeks	4 weeks	8 weeks	4 weeks	12 weeks
Enrolment						
Eligibility screen	X					
Informed consent	X					
Medical history	X					
Allocation		X				
Interventions						
Acupuncture		X	X	X		
Sham acupuncture		X	X	X		
Assessments						
Primary outcome						
PSQI		X	X	X	X	X
Secondary outcomes						
ISI		X		X		
Actigraphy		X		X		
SDS		X		X		
SAS		X		X		
Men-QoL		X	X	X	X	X
Others						
Estazolam dose		X	X	X	X	X
Adverse events		X	X	X	X	X
Patients’ satisfaction						X
Success of blinding						X

### Recruitment

Participants of the study will be recruited through the outpatient clinic, hospital-based Wechat advertising, and posters in Shanghai Municipal Hospital of Traditional Chinese Medicine in Shanghai, China. Those who are interested in participating in the study will be screened either via telephone or on-site. They will receive eight weeks of acupuncture treatment or sham acupuncture and a series of assessments on sleep disorders free of charge. During the study, participants will be required to wear a wrist Actigraphy to record their sleep quality. The participants who meet the inclusion criteria will be informed of the research details and asked to sign the informed consent before the treatment commence. The research assistant will obtain informed consent from participants.

### Inclusion criteria

Participants with the following conditions will be included:Menopausal women aged 45~60 years;Participants who meet the diagnostic criteria of TCM in accordance with the above perimenopausal and insomnia [22];Participants in line with the international classification of sleep disorders (ICSD-3) for the diagnosis of insomnia;Participants whose PSQI score is > 5;Participants who voluntarily agree to join the study and to sign the written informed consent form for the randomized controlled trial (RCT).

### Exclusion criteria

Participants with the following conditions will be excluded:Participants who have severe mental illness such as depression, anxiety, schizophrenia, etc.;Participants with serious heart, brain, kidney, or liver disease;Participants with secondary insomnia caused by systemic diseases such as pain, fever, cough, surgery, and external environment disturbances;Participants who have taken hormones for ≥ 6 months;Participants who are pregnant or currently lactating.

### Intervention

Participants in each group will receive 18 real or sham treatments within an eight-week period. In each group, they will receive either acupuncture or sham acupuncture treatment three times per week for the first four weeks, twice per week for the next two weeks, and once per week for the last two weeks. Each treatment will last for 30 min. Each patient will then be placed in a separate quiet space and lying supine. The acupuncturists will be registered practitioners with > 3 years of experience in acupuncture practice. In order to increase the patients’ compliance, they will accept the intervention and assessment by reservation and they will receive some financial subsidies (200 RMB) after the follow-up assessments.

In the treatment group, acupuncture needles will be standard stainless steel, sterile, and disposable (0.25 × 40 mm and 0.30 × 40 mm in length; Jia Jian, China). The control group will use the Streitberger Placebo-needle at the same acupoints. The treatment methods of acupuncture and acupoints are shown in Table 2.

**Table 2 Tab2:** Details of intervention

	Intervention group	Control group
Main acupoints	GV20, GV24, GV29, RN6, RN4, SP6, HT7, EX-HN22	GV20, GV24, GV29, RN6, RN4, SP6, HT7, EX-HN22
Added acupoints	Kidney yang deficiency GV4, BL23	Kidney yang deficiency GV4, BL23
	Kidney yin deficiency KI3, KI7	Kidney yin deficiency KI3, KI7
Depth of insertion	GV20, GV24, GV29, RN6, RN4, EX-HN22 10 mm	No insertion
	HT7, SP6, GV4, BL23, KI7, KI3 15 mm	
Needle type	Steel needle (Wuxi Jiajian Medical Co. Ltd., Wuxi, China)	Blunt-tip needle (Streitberger Placebo-needle)
Needle sensation	With de-qi sensation	Without de-qi sensation
Electric stimulation	Needle on GV20, GV29 connected to G6805–2 Multi-Purpose Health Device (Shanghai Medical Instruments High-Techno, China) with electric pulse at a frequency of 2.5 Hz and an intensity of 45 mA	Needle on GV20, GV29, connected to G6805–2 Multi-Purpose Health Device (Shanghai Medical Instruments High-Techno, China) without electric pulse
Frequency and duration	Three times per week for the first four weeks	Three times per week for the first four weeks
	Twice per week for the next two weeks	Twice per week for the next two weeks
	Once per week for the final two weeks	Once per week for the final two weeks

### The acupuncture group

Participants in this group will receive acupuncture treatment during the first eight weeks. According to our in-depth research on insomnia and acupuncture experience, Baihui (GV20), Shenting (GV24), Yintang (GV29), Qihai (RN6), Guanyuan (RN4) and bilateral Anmian (EX-HN22), Sanyinjiao (SP6), and Shenmen (HT7) will be used as main acupoints [17]. Acupuncturists will be permitted to add acupuncture points based on TCM syndrome differentiation [23]. According to our own clinical practice, potentially relevant extraneous points include Mingmen (GV4) and Shenshu (BL23) for kidney yang deficiency and TaiXi (KI3) and Fuliu (KI7) for kidney yin deficiency. The needles will be inserted into the skin to the depth of 10–30 mm and manipulated manually (including lifting, thrusting, and rotating) until the patient reports needling sensations (Deqi sensation). The needles on GV20 and GV29 will be connected to a G6805–2 Multi-Purpose Health Device (Huayi Company), using continuous wave type, frequency at 2.5 HZ, and intensity of 45 mA. Needles will be retained for 30 min before removal.

### The control group

Participants in this group will receive sham acupuncture treatment. We will use a non-invasive placebo control, the Streitberger Placebo-needle. Acupoints are the same as with acupuncture group, without insertion. An electroacupuncture apparatus (G6805–2 Multi-Purpose Health Device) will be set beside the patients and connected to the GV20 and GV29, without electrical pulse. Needles will be also retained for 30 min before removal.

### Outcome measures

We will assess the primary outcome at baseline, week 4, week 8, after treatment, and with follow-ups at week 4 and week 12 after the end of treatment. Secondary outcomes will be assessed at baseline and week 8.

### Primary outcome

#### Pittsburgh Sleep Quality Index (PSQI)

The PSQI is a self-rated questionnaire used to measure general sleep quality. It comprises 19 self-rated items and five other-rated items [20]. It assesses sleep based on seven domains in the past month: sleep duration; sleep disorders; sleep-onset latency; daytime dysfunction; sleep efficiency; use of medications to sleep; and overall sleep quality [24]. Each domain is rated 0–3; the accumulated scores of the seven domains constitute the total score of the PSQI (0–21). A total score of > 5 indicates a poor quality of sleep [25] .

### Secondary outcomes

#### Insomnia Severity Index (ISI)

The ISI is designed to assess the nighttime and daytime symptoms of insomnia. It includes seven items rated on a scale of 0–4 points; the total score is in the range of 0–28 [26]. All self-reported questionnaires are conducted in Chinese. A higher score indicates a more severe insomnia. ISI classification: clinical insomnia (score 0–7), mild insomnia (score 8–14), moderate insomnia (score 15–21), and severe insomnia (score 22–28).

#### Actigraphy assessments

The wActiSleep-BT actigraph (Actigraph LLC, Pensacola, FL, USA), will be worn on the patients’ wrist, which can record the sleep quality by noting sleep awakenings (SA), total sleep time (TST), sleep onset, sleep latency as well as the efficiency of sleep. The analysis of sleep condition and sleep quality will be performed by the software ActiLife6 (Version 6.8.1, Actigraph LLC) [17, 20].

#### Self-Rating Anxiety Scale (SAS)

We will use SAS to assess the degree of anxiety in patients. The questionnaire includes 20 items, as follows: 15 negative and five positive descriptions, the opposite of the score [27]. The total score of the 20 items is > 40 points, indicating the state of anxiety. A higher score indicates more severe anxiety.

#### Self-Rating Depression Scale (SDS)

The SDS is a self-rated scale for evaluating the severity of depression [28]. The main statistical index consists of 20 questions. We first calculate the standard score by ranking the participant’s responses to 20 questions. From this figure, the total score determined as is 1.25 times the standard score, making use of the integral part [17]. The demarcation point of depression is 50 points, the higher the score, the more significant the depression tendency.

#### Menopause Quality of Life (MenQOL)

MenQOL is a questionnaire used to assess the quality of life in menopause, including 29 items, which are divided into four domains: Vasomotor (Items 1–3); Psychosocial (Items 4–10); Physical (Items 11–26); and Sexual (Items 27–29). For analyses, we convert the item scores to a score in the range of 1–8 (NO, 0–6). Each domain mean is in the range of 1–8. The overall questionnaire score is the mean of the domain means. A higher score indicates a worse quality of life [29].

#### Estazolam dose

Patients will be allowed to take Estazolam (0.5–2.0 mg) when they have difficulty in falling asleep for > 3 consecutive days during the trial. They will be asked to record the dose and the time of taking Estazolam on the case report form (CRF).

#### Sample size

The sample size calculation was based on the change of PSQI scores. Systematic review [21] shows that at least a 2.70-point difference in PSQI scores between acupuncture and sham acupuncture has clinical significance. We expected that acupuncture would outperform the sham acupuncture by 3 points; therefore, a sample size of 35 participants should be recruited in each group. Considering a dropout rate of ~ 20%, each group will take 42 cases. Therefore, a total of 84 participants should be recruited for this RCT.$$\mathrm{N}=2\ast \kern0.5em {\left[\frac{\left({U}_{\upalpha}+{U}_{\upbeta}\right)\upsigma}{\updelta}\right]}^2;\kern0.5em \left(\upalpha =0.05,\upbeta =0.2\right)$$

#### Randomization and allocation concealment

We will use the block randomization method. We plan to use SPSS version 23.0 software to generate a random number table. The participants who meet the criteria will be randomly assigned to acupuncture group or control group with 1:1 ratio. The random allocation sequence will be generated in a block. The block size will be randomized to six.

The treatment allocation codes will be enclosed in sequentially numbered opaque envelopes by an independent researcher; the research assistant will pick the envelope and give it to the acupuncturist when the participants have finished all baseline assessments and immediately begin the first acupuncture treatment. The principal investigator (PI), co-investigators (Co-Is), and independent outcome assessors will be blinded to the treatment assignment. Only the acupuncturists will know to which groups the participants belong.

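### One published block size of six, at one site with unblinded acupuncturists, is an avoidable weakness in allocation concealment

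*Protocol article*

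**What the plan says.** In the protocol article, the section Randomization and allocation concealment specifies block randomization, with participants "randomly assigned to acupuncture group or control group with 1:1 ratio". On the structure of the list it says "The random allocation sequence will be generated in a block" and then "The block size will be randomized to six". It gives no other size, no set of sizes and no stratification factor. The Design section gives one site, and the Sample size section gives 84 participants.

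On who knows what, the randomization section says "Only the acupuncturists will know to which groups the participants belong", and the Blinding section repeats this. An independent researcher prepares opaque envelopes numbered in sequence. After all baseline assessments, "the research assistant will pick the envelope and give it to the acupuncturist", and the first session follows at once. Under Recruitment, "The research assistant will obtain informed consent from participants". The Intervention section says that visits are made by reservation.

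**The concern.** A block size drawn at random needs at least two candidate values, so the sentence cannot be taken literally. If it means that every block has six places, each block holds three acupuncture and three sham assignments. Once three of either kind have been used, the rest of the block is known. Opaque envelopes hide a single code, but they do not hide the end of a block whose length is public.

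The setting makes this more relevant than usual. There is one sequence, and the treating staff learn each allocation as it is opened. The role that obtains consent is also the role that hands them the envelopes. If knowledge of the next allocation reached someone who decides who enters or when, entry could be timed by expected response. The primary analysis is a t test on the change in a self-rated score (PSQI), and blinding of participants, assessors and analysts after allocation would not undo a selection made before it.

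**Working it through.** The article states no predictability figure, so there is none to reproduce. The check asks how much a fully informed observer could predict.

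**Inputs.** Block size 6 and ratio 1:1, hence 3 + 3 per block (Randomization and allocation concealment); 84 participants (Sample size); one site (Design), taken as one sequence because no stratification is mentioned. Number of blocks: 84 / 6 = 14, all complete.

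**Certain assignments, fixed size six.** There are C(6,3) = 20 equally likely blocks. An assignment is certain once one arm's three places are used up.

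- 12 blocks end with 1 certain assignment, 6 with 2, and 2 with 3.
- Mean per block: (12×1 + 6×2 + 2×3) / 20 = 30 / 20 = 1.5.
- Share: 1.5 / 6 = 25.0%. The closed form for a block of 2m, 1/(m+1), gives 1/4 for m = 3.
- Whole trial: 14 × 1.5 = 21 of 84 expected. Simulation of 14 blocks gives a 95% range of 16 to 26. The minimum is 14, because the last place in every block is always certain.

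**Best guess, fixed size six.** The observer always names the arm with more places left. The chance of being right at places 1 to 6 is 0.5, 0.6, 0.6, 0.7, 0.7 and 1.0. The sum is 4.1, and 4.1 / 6 = 68.3%, against 50% with no information.

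**Varying sizes.** These were simulated for an observer who knows the set of sizes and all past allocations, but not where blocks begin and end.

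| Block sizes | Certain | Best guess correct |
|---|---|---|
| 6 fixed | 25.0% | 68.3% |
| 4, 6 | 5.4% | 69.1% |
| 2, 4, 6 | 4.2% | 70.2% |
| 6, 8 | 4.0% | 67.1% |
| 4, 6, 8 | 2.3% | 67.9% |

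Two results follow. If the sentence meant sizes varying up to six (rows 4, 6 and 2, 4, 6), the certain share is about 4 to 5%, not 25%. And varying the size removes most certain predictions but leaves the best guess almost unchanged.

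**The case against.** A reader might infer that a quarter of this trial's assignments will in fact be predictable, and that selection bias follows. The documents do not support that, for four reasons.

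- **The observer.** The 25% needs one person who knows the size and sees the full sequence in order. The article speaks of acupuncturists in the plural and does not say that any one of them treats everyone or that they share allocations.
- **The link to entry.** Bias needs knowledge of past allocations together with influence over who enters or when. Consent and envelope handling belong to the research assistant, and researchers other than the acupuncturists are to be blinded. No section gives acupuncturists a part in screening, consent or booking. That one individual fills the research assistant role throughout is also an inference; the text shows only that the same role is named in both places.
- **The safeguards.** Envelopes are prepared independently and handed over only after baseline assessments. Table 1 puts eligibility and consent one week before allocation, so the next code at the time of consent need not be the one that participant receives.
- **The wording.** The sentence may be poor English for sizes varying up to six.

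It can be added that a condensed article may leave the withholding of block details to the full protocol.

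The first three objections stand against any claim of actual bias. They do not remove the weakness: the envelope handover brings the consenting role into contact with staff who know past allocations, and booking by reservation leaves some room over the order of first visits. The fourth stands as a limit on the figure, but six is the only size named, and the sentence needs correcting on either reading. The last does not answer the point, since the article itself states the size.

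**Conclusion.** The point holds as an avoidable weakness in concealment, and the sponsor should correct it. The expected share of certain assignments is 25%, about 21 of 84. This assumes that the size is fixed at six, that there is one unstratified sequence, and that the observer knows the size and sees all past allocations in order. It is lower for an acupuncturist who sees only their own patients; the documents do not say how allocations divide among acupuncturists, so that figure cannot be calculated.

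The 68.3% best-guess figure should not be read as harm that varying block sizes would remove, since it is nearly the same under every scheme in the table. Nor does anything here show that participants would be selected. The documents show a route that should be closed, not its use.

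**What to change.** Before the list is generated:

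1. Replace the block-size sentence with randomly varying sizes, for example 4, 6 and 8, known only to the independent researcher who prepares the envelopes. For the observer modelled above, the expected number of certain assignments falls from 21 to about 2 of 84 (84 × 0.023 = 1.9).
2. State that acupuncturists take no part in screening, consent or the scheduling of first visits, and do not disclose past allocations to the research assistant. The second step is needed because the first leaves best-guess accuracy near 68%.

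The cost is small. The Trial status section describes the trial as still in preparation, so this means writing a new list and two or three sentences of text. With sizes of 4, 6 and 8 the last block may be incomplete at 84, so the exact 42:42 split is no longer guaranteed. The arms could differ by at most half the largest block, 8 / 2 = 4 participants, which matters little for the comparison.
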